# Foot exercise plus education versus wait and see for the treatment of plantar heel pain (FEET trial): a protocol for a feasibility study

**DOI:** 10.1186/s13047-020-00384-1

**Published:** 2020-05-08

**Keywords:** Plantar fasciitis, Exercise therapy, Rehabilitation, Intrinsic foot muscles, Physiotherapy, Randomised control trial

## Abstract

**Background:**

Plantar heel pain (PHP) is present in a wide range of individuals and creates significant burden to quality of life and participation in physical activity. The high recurrence rates and persistence of PHP suggests current management options may not address all potentially modifiable factors associated with the condition. Reports of intrinsic foot muscle (IFM) atrophy in individuals with PHP, together with biomechanical evidence of their important contribution to optimal foot function, suggests that an intervention focused on IFM training may be beneficial in managing PHP. We will test the feasibility of a prospective, assessor-blinded, parallel-group, randomised clinical trial that compares foot exercise plus education to brief advice in individuals with PHP.

**Methods:**

Twenty participants with PHP will be randomly allocated to one of two groups for a 12-week intervention period: (i) foot exercise plus education, or (ii) brief advice. The foot exercise plus education group will attend eight sessions with a physiotherapist and receive detailed education on self-management strategies as well as a progressive exercise program for the IFMs. The brief advice group will attend one session with a physiotherapist and receive brief information about self-management strategies and reassurance. Outcome measures will be obtained at baseline and the primary end-point of 12 weeks. Primary outcomes will be the feasibility of conducting a full-scale randomised clinical trial (RCT), and the credibility and acceptability of the foot exercise plus education intervention. Secondary outcomes will explore treatment effects, which will consist of pain, physical function, physical activity level, pain self-efficacy, perceived treatment effect, magnetic resonance and ultrasound image measurement of IFM morphology, ultrasound imaging measurement of plantar fascia thickness, IFM motor performance, foot posture, foot mobility, ankle dorsiflexion range of motion, toe flexor and plantar flexor strength/endurance.

**Discussion:**

To reduce the burden of PHP on individuals and society, there is a need to establish effective treatments that are feasible and accepted by patients and health professionals. This trial will be the first to evaluate the feasibility of conducting a full-scale RCT, as well as the credibility, acceptability, and treatment effects, of education and foot exercise for PHP. The findings of this study will inform the development of a full-scale RCT.

**Trial registration:**

The trial protocol was prospectively registered with the Australia and New Zealand Clinical Trial Registry (ACTRN12619000987167) on 11th July 2019.

## Background

Plantar heel pain (PHP) is a common musculoskeletal disorder characterised by pain at the plantar aspect of the medial heel, most noticeable on weight bearing after a period of inactivity but also worse following prolonged weight bearing [1]. PHP affects a wide spectrum of individuals from the sedentary to the physically active/athletic individual. Prevalence rates vary between 3 and 18% among different populations [2–8]. Low physical activity and higher rates of anxiety, depression and stress are reported by individuals with PHP, highlighting the significant burden of the condition beyond pain [2, 9]. Despite the common description of PHP as a ‘self-limiting’ disorder, a longitudinal study with an average follow-up of 10 years reported that 53% of individuals experienced relapse of symptoms in that time, and 46% had persistent symptoms [10]. This suggests that current management options do not adequately address symptoms and impairments associated with the condition, nor address potential contributors to ongoing symptoms.

During walking and running the foot dissipates, recycles and produces mechanical energy [11]. This involves contributions from both the passive (i.e. plantar fascia, heel fat pad, ligaments and bone) and active (i.e. intrinsic and extrinsic muscles) structures of the foot. The intrinsic foot muscles (IFMs) have all their anatomical attachments within the foot, as opposed to the extrinsic muscles that originate in the leg. The IFMs have been shown to assist damping of energy associated with foot-ground impact and play a critical role in stiffening the foot for propulsion [12, 13]. The distinguishing contribution of the IFMs (compared to passive structures) is the ability to actively modulate the energetic function of the foot to respond to changing demands (e.g. acceleration/deceleration, surface, and footwear, etc.) [11, 14].

Muscle morphology is a primary determinant of muscle function [15]. Atrophy of the IFMs has been reported in PHP. A previous study that used magnetic resonance imaging (MRI), the gold-standard for evaluation of muscle morphology, reported smaller rearfoot muscle volume in runners with persistent PHP when compared to asymptomatic runners [16]. The IFMs were segmented as a muscle group (not individual muscles) by excluding all non-contratile tissues on each image. IFM volume was then calculated by summing the product of slice thickness and IFM cross-sectional area for each image. Forefoot and rearfoot volumes were determined from the anterior or posterior half of the full image set, respectively, and therefore also represent morphology of a region rather than individuals muscles. Due to the cross-sectional design of previous research, the causal relationship between IFM morphology and PHP is unknown. It is possible that IFM atrophy contributes to the development of PHP. For example, atrophy of these muscles may compromise the energetic function of the foot with implications (e.g. modified loading) for passive structures such as the plantar fascia, heel fat pad and calcaneus. It is also plausible that IFM atrophy is a consequence of PHP. For example, IFM atrophy may occur due to the presence of pain and/or altered foot and physical function. The significant contribution of the IFMs to the energetic function of the foot suggests that IFM atrophy is important to address in the management of PHP.

Three studies have evaluated interventions for PHP that have included IFM training [17–19]. Two of these studies [18, 19] have investigated 4 weeks of multimodal interventions where IFM exercise was combined with manual therapy, electrotherapy, stretching and/or medication. In these studies, as IFM exercise was a component of a combined package of interventions, and was included in the intervention for both comparator groups, the effect of IFM training is difficult to determine. The other study [17] investigated the addition of IFM exercise to calf stretching over 8 weeks and reported no difference when compared to calf stretching alone. In that study, there were several limitations that may have influenced the effectiveness of the IFM exercise programme. For example, there were only two exercises that targeted the IFMs (toe curl exercise and short foot exercise) that were performed under supervision of a physiotherapist for 8 weeks (16 sessions in total). The toe curl exercises were performed for 3 sets of 15 repetitions with graduated resistance of 1 and 2 kg weights and the short foot exercise for 3 one-minute isometric holds in single limb stance. The exercise programme was likely insufficient for hypertrophy/strength gains [20], but it remains unknown, as there was no measurement of IFM structure and/or strength. Two other studies in healthy populations, have reported increased IFM size (10–21%) and strength (35–106%) with a programme that involved more than two foot exercises, at higher intensities and larger volumes [21, 22]. IFM training with sufficient volume, intensity and progression may produce more beneficial results in PHP compared to previous trials.

The primary aim of this study is to investigate the feasibility of conducting a full-scale randomised clinical trial (RCT), as well as the credibility and acceptability of a foot exercise plus education intervention in individuals with PHP. The secondary aim is to investigate treatment response (effect sizes) using a comprehensive set of measurements which consists of pain, physical function, physical activity level, pain self-efficacy, perceived treatment effect, MRI and ultrasound image measurement of IFM morphology, ultrasound imaging measurement of plantar fascia thickness, IFM motor performance, foot posture, foot mobility, ankle dorsiflexion range of motion, toe flexor and plantar flexor strength/endurance.

## Methods

### Design

This protocol describes a feasibility study of a prospective, assessor-blinded, randomised clinical trial with two parallel groups and a 12-week intervention period (Fig. 1). Participants will be randomised to each group using a 1:1 ratio (see ‘Allocation’ for more detail regarding randomisation). The primary end point is 12 weeks. The trial will be conducted in physiotherapy clinics in Brisbane, Australia and The University of Queensland. This study protocol follows the Standard Protocol Items: Recommendations for Interventional Trials (SPIRIT) guidelines [23]. The trial was prospectively registered with the Australia and New Zealand Clinical Trial Registry on 11th July 2019 (ACTRN12619000987167; http://www.ANZCTR.org.au/ACTRN12619000987167.aspx).

**Fig. 1 Fig1:**
[figure not shown]
Study design

### Ethics approval

Ethical approval was obtained from The University of Queensland’s Human Research Ethics Committee (#2019000772). Prior to enrolment in the trial, all participants will provide informed written consent.

### Participant recruitment

Potential participants will be recruited from the Brisbane community using social media (Facebook) and public advertisements (University and community noticeboards).

### Eligibility criteria

A three-stage screening process (online survey, telephone interview, physical screening) will be used to assess eligibility of volunteers who respond to advertisements. The advertisement will direct volunteers to an online survey link (Google forms) or to contact the chief investigator (email, phone). The online survey link will assess preliminary eligibility criteria (e.g. age, pain characteristics and concomitant conditions, see Additional File 1). For volunteers who directly contact the chief investigator, the preliminary eligibility criteria will be covered within the telephone interview. Telephone interviews and physical screenings will be conducted by the chief investigator (see Additional File 2), a registered physiotherapist with 15 years of experience. The telephone screening will assess eligibility criteria in more detail and describe the purpose of the study and participant involvement in more detail. Volunteers who fulfil all eligibility criteria, and are able to commit to participation in the trial, will be invited to attend a physical screening at The University of Queensland. The physical screening will involve palpation of the plantar fascia and medial calcaneal tubercle and ultrasound image measurement of plantar fascia thickness.

#### Inclusion criteria

Volunteers will be included if they satisfy the following criteria.
Over 18 years of age.Report a history of insidious onset pain under the sole of the foot, located at the heel, that has persisted for more than 3 months.Report pain that is most noticeable with initial steps following a period of inactivity, and also worsened with prolonged weight bearing [1].Report worst first step pain during the previous week of greater than 3/10 on a numerical rating scale (0 = no pain; 10 = worse pain imaginable).Report pain on palpation of the medial calcaneal tubercle or proximal fascia.Plantar fascia thickness is 4 mm or greater when measured using ultrasound imaging.

### Exclusion criteria

Volunteers will be excluded if they report a history of the following:
Diabetes or an inflammatory systemic disease.Concomitant foot injury or pathology.Previous foot surgery.Pain or an injury of the lower back or lower limb (other than heel pain) in the preceding 6 months that caused them to seek medical assistance or treatment, take medication, miss work or reduce physical activity for at least 1 week.Currently pregnant or breastfeeding.Have received a corticosteroid injection in the foot during the preceding 6 months.Contraindications to undergoing MRI (e.g. metal implants or pacemaker, etc.).

### Informed consent

Volunteers who meet the eligibility criteria will be provided with a participant information and consent form and given the opportunity to ask any questions of the chief investigator. Eligible volunteers who decide to participate will provide written informed consent and a baseline assessment session will be scheduled.

### Allocation

Following baseline assessment, participants will be randomised via concealed allocation to either foot exercise and education or wait and see (brief advice). A computer generated randomization schedule will be used, allocating on a 1:1 ratio in random permuted blocks of 2–6 [24]. A study investigator (RM) who is not involved in recruitment or outcome assessment will manage the randomisation allocation and liaise with the treating physiotherapist regarding group allocation. As treating physiotherapy clinics are located in various suburbs of Brisbane, participants may select the most convenient practice for them to attend. Participants will be informed of group allocation by the treating physiotherapist.

The interventions will be delivered by registered physiotherapists, who regularly treat musculoskeletal conditions, in seven private practices across Brisbane. To ensure consistent implementation of both interventions, treating physiotherapists will attend 2 training sessions of 90-min duration each, 1 week apart, at The University of Queensland prior to commencement of the trial. Trial physiotherapists will also be provided with a trial handbook (detailed documentation including images, instructions and progressions of exercises) and advised to contact the study investigators for any queries that arise during the trial.

### Interventions

#### Foot exercise plus education

Participants allocated to this group will attend eight individual physiotherapy sessions (weeks 1,2,3,4,5,6,8 and 10) during the 12-week intervention period. Physiotherapy sessions will be 30 min duration and will include detailed education relating to the condition and self-management strategies, as well as an exercise program that will be performed both at home and supervised by the physiotherapist during sessions. Participants will be asked to complete a daily logbook (Additional file 3) of exercises that are completed, symptoms, any physical activity that is undertaken, adverse responses and details of any treatments they have outside of the study protocol.

The 12-week foot muscle focussed training programme will consist of two components: exercises performed daily and exercises performed three times a week. Table 1 provides an overview of the exercise programme and Additional file 4 provides the detailed exercise protocol, including specific instructions for each exercise. Daily exercises will consist of four foot and toe movements and two weight bearing exercises. Exercises performed three times a week will consist of four exercises, each with three stages of progression. Progression is provided by varying the number of repetitions and sets, amount of load and rate of loading. Participants will progress through the stages 1 to 3 in an individualized, criterion-based manner. When the indicated repetitions and sets are reached for a stage, progression is made provided that:
(i)the therapist considers that the patient can adequately recruit the IFMs without excessive extrinsic foot muscle contribution (e.g. able to maintain extension of the interphalangeal joints of the toes) or perform local joint motion at the foot and ankle with optimal control (i.e. smooth motion through the intended plane of action without unintended overflow into adjacent planes or joints, such as, pronation or supination of the foot and ankle);(ii)the participant’s rating of effort of each exercise using Modified Borg Scale is 0–5/10;(iii)the participant’s pain response to loading is adequate (pain during exercise < 5/10 on a numerical rating scale and no change in first step pain the following day).

**Table 1 Tab1:**
[figure not shown]
Exercise programme

*s* seconds; *reps* repetitions

The education component will include information about the condition and self-management strategies. Information about the condition will outline that PHP is a description of symptoms, and that there can be several structures involved and common contributing factors. Self-management advice will explain how to monitor load and symptom response and advice regarding footwear, posture and gait. This will be delivered one-on-one by the physiotherapist at the first session and supported by the provision of a handout detailing the information discussed with the physiotherapist (Additional file 5). Review and reinforcement of self-management strategies will be included at each subsequent physiotherapy sessions.

#### Wait and see (brief advice)

Participants allocated to this group will attend one individual (one-on-one) physiotherapy session during the 12-week intervention period (week 1). The session will be 30 min duration and consist of the therapist providing brief information about the condition and advice on how to self-manage the condition (e.g. common contributing factors, modifying daily activities to within acceptable pain levels and gradual progressions in activity within pain limits, etc.). Participants will be reassured that in many people symptoms can resolve over time (12–24 months) and that currently there is no gold standard treatment approach supported by scientific evidence. The physiotherapist will take time to listen to any patient concerns regarding their condition. Information will be supported by provision of a simple handout (Additional file 6). Participants will receive no additional treatment during the 12-week intervention period. Participants will be asked to complete a weekly logbook of symptoms, any problems that are encountered (related to their heel pain) and any treatments outside of the study protocol (Additional file 7).

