#### Adverse events

Participants will be encouraged to report any untoward health/medical related events (i.e. adverse events) regardless of likely cause. This will include possible adverse reactions (e.g. increase in heel pain, onset of new pain or injury elsewhere) that they experience during the study to a study investigator (RM) and/or their physiotherapist. If an adverse event is associated with the foot exercise plus education intervention, the physiotherapist will modify the exercise prescription and/or load management advice accordingly until a reduction in symptoms is reported. In the event of a sustained increase in heel pain or aggravation of another area of pain, standard clinical practice principles will apply and provision of any treatments outside of the study protocol (e.g. taping) will be recorded in the physiotherapist’s treatment notes and reported to a study investigator (RM). If symptoms associated with the adverse event are unable to be resolved, the intervention will be ceased and the participant encouraged to remain in the trial to enable follow-up data collection.

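### Adverse events are prompted more often and more broadly in the exercise arm than in the control arm, so the by-arm counts are not directly comparable

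*Protocol article*

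**What the plan says.** All references are to the protocol article.

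- **Foot exercise plus education.** Participants "will attend eight individual physiotherapy sessions (weeks 1,2,3,4,5,6,8 and 10) during the 12-week intervention period". They also keep a daily logbook that covers, besides the exercises done, "symptoms, any physical activity that is undertaken, adverse responses and details of any treatments they have outside of the study protocol".
- **Wait and see (brief advice).** Participants have a single session, in week 1. "Participants will be asked to complete a weekly logbook of symptoms", together with "any problems that are encountered (related to their heel pain) and any treatments outside of the study protocol".
- **Adverse events.** All participants are "encouraged to report any untoward health/medical related events (i.e. adverse events) regardless of likely cause". The section counts pain or injury at another site as a possible adverse reaction. Reports go to a study investigator, the physiotherapist or both. Treatments given outside the protocol for a sustained aggravation are entered in the physiotherapist's notes.
- **Primary outcome measures.** Adverse events are the seventh feasibility item. Additional treatments sought are an acceptability item, assessed for both interventions.
- **Statistical analysis.** Primary outcomes are summarised descriptively. Between-group differences are planned for the secondary aim.
- **Discussion.** The one-versus-eight session imbalance is acknowledged as a source of performance bias. Its effect on the recording of events is not mentioned.

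**The concern.** The protocol defines adverse events broadly, but the logbooks described for the two arms do not collect them in the same way. A control participant who develops, say, knee pain has no logbook item asking for it and no scheduled physiotherapist contact after week 1. An exercise participant with the same complaint has a daily item without a stated site limit and up to seven further sessions at which to mention it.

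The adverse-event and additional-treatment counts are components of the primary outcomes and are meant to inform a full-scale trial. With 10 participants per arm, one or two extra recorded events could change the impression of safety carried forward. If those extra events come from closer questioning, the exercise programme would look less well tolerated than it is, relative to brief advice.

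**Working it through.** The plan gives no figure on this point to reproduce. The check has three parts.

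**1. Scheduled recording opportunities over 12 weeks** (from the two intervention sections)

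| Source | Exercise | Control | Ratio |
|---|---|---|---|
| Logbook entries | 12 × 7 = 84 | 12 × 1 = 12 | 7.0 |
| Physiotherapy sessions | 8 | 1 | 8.0 |
| Total | 92 | 13 | 92 / 13 = 7.1 |

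**2. What is asked, set side by side**

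| Item | Exercise | Control | Difference |
|---|---|---|---|
| Adverse events, logbook | Adverse responses, no stated site limit | Problems tied to heel pain | Scope and interval |
| Outside treatments, logbook | Any | Any | Interval only |
| Scheduled physiotherapist contact | 8 sessions | 1 session | Number of contacts |
| All-cause voluntary report | Yes | Yes | None in the rule |

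In the control logbook sentence the parenthesis follows the word for problems and precedes the separate clause on treatments, so it limits only the former. Adverse events therefore differ in scope, interval and contact. Outside treatments differ only in interval and contact.

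**3. How large a spurious difference could be (illustration on assumed inputs)**

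Suppose the true proportion *p* of participants with at least one event is the same in both arms, and an event is detected with probability *d*. The expected observed difference is *p* × (*d* exercise − *d* control). Neither *p* nor *d* is in the document. Taking *d* = 0.9 in the exercise arm:

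| True *p* | Control *d* = 0.9 | Control *d* = 0.7 | Control *d* = 0.5 |
|---|---|---|---|
| 0.20 | 0 | 0.20 × 0.2 = 4 points | 0.20 × 0.4 = 8 points |
| 0.40 | 0 | 8 points | 16 points |
| 0.60 | 0 | 12 points | 24 points |
| Ratio of observed proportions | 1.0 | 0.9 / 0.7 = 1.29 | 0.9 / 0.5 = 1.8 |

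With 10 per arm this is 0 to 2.4 participants. The result depends wholly on the detection probabilities assumed.

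One further detail bears on the check. Logbook completion is defined by training sessions recorded. Controls have none, so the stated metric would not reveal how fully the control logbooks were kept.

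**The case against.** The case on the other side is substantial, and much of it stands.

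- **There is a common all-cause route.** Any participant can report any event to an investigator without a visit. A reader might infer that control events away from the heel go unrecorded. The document does not support that; such events lack only a logbook prompt. However, a voluntary route open to both arms does not cancel extra prompting in one.
- **Outside treatments are asked about without restriction in both logbooks.** A reader might extend the heel limit to treatments, but the wording does not allow it. A participant is also unlikely to forget within a week that treatment was sought, so the problem is weaker here.
- **No formal between-arm comparison of these items is planned.** To say that the comparison is biased, or that the results are uninterpretable, goes too far. The exercise-arm counts can still be read on their own. Descriptive counts shown by arm will nevertheless be read against each other, and unequal collection affects them as it would affect a test.
- **The 7 to 1 ratio is not a bias estimate.** Twelve weekly entries cover the same 12 weeks as 84 daily ones, and nothing says that each session includes a structured enquiry about events.
- **The instruments are not shown.** The logbooks (Additional files 3 and 7) and the 12-week interview guide (Additional file 8) may contain fuller or common questions. The exercise item could also be read as reactions to the exercises rather than all events. What the main text says about interval and scope is nonetheless explicit, and it differs by arm.

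**Conclusion.** The point holds for prompted ascertainment. The exercise arm is asked more often about adverse events and without a stated site limit. The control logbook prompt is narrower than the protocol's own definition. By-arm counts of adverse events are therefore not directly comparable, and counts of additional treatments are less comparable than they appear. The likely direction is more recorded events under exercise. The size cannot be derived: the illustration runs from no difference to 24 percentage points, on assumed detection rates.

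The conclusion rests on the article's description of the logbooks matching the forms in use, and on no common all-cause question having been put to both arms at 12 weeks. Either additional file could soften it. It does not extend to a claim that exercise will necessarily show more events, or that the safety data cannot be used.

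**What to change.** **For the full-scale trial**

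- Put one identical weekly page in both logbooks with two all-cause items: any new or worse health problem, anywhere; and any treatment outside the study. The daily exercise log can stay for adherence.
- Ask both arms the same open question at 12 weeks. Someone other than the blinded assessor should ask it, for example the investigator who manages allocation and already receives adverse event reports.
- Base any side-by-side comparison on this common source. List events from the daily log and from sessions separately, labelled by source.

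**For this trial**

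The Trial status section puts the last follow-up measurement on 31 January 2020, so only reporting can change.

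- Report events by source.
- Limit side-by-side comparison to heel-related problems and outside treatments, aggregated by week. This narrows the imbalance but does not remove it, because daily entries still have shorter recall.
- List all other events descriptively and state that they are not comparable between arms.
- Extend the Discussion's remark on unequal contact to cover ascertainment as well as performance.

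**Cost.** One page in an existing form and one question at an existing time point; for the completed trial, wording only. The downside is that fewer events enter the comparative table.
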